### Randomization

Consecutive eligible patients are randomly allocated in a 1:1 ratio to one of the two treatment groups: vaginal progesterone or cervical pessary. The randomization sequence is computer generated (by EpiDat program). It is protected and it is managed exclusively by the Clinical Pharmacology Unit at University Hospital Puerta de Hierro - Majadahonda, which has no role in recruitment. The investigators receive the patient’s identification (ID) number and the assigned treatment by a central phone call, after having been informed that a new patient has entered into the trial. An auditable registry of the date and time of inclusion, patient ID number and treatment assignment is stored in the sponsor’s records.

### Study interventions

Two accepted treatments in the management of preterm birth risk are being assessed in the PESAPRO trial, although neither of them is approved for use in this condition. For statistical purposes, we consider the pessaries to be the experimental group and progesterone to be the reference (or comparator) group. Patients who are assigned to the comparator group receive 200 mg of micronized progesterone per day by vaginal route; women self-administer the medicine once daily, preferably before going to bed.

The cervical pessary used in this study is a perforated-cerclage type pessary, a hypoallergenic silicon medical device certified by European Conformity, size 65/25/32 (65 mm lower larger diameter, 25 mm height and 32 mm upper smaller diameter). The pessary is disposed of (and removed) by qualified personnel (Obstetrician) at the clinic. Both treatments are withdrawn between the 37th week and 37 week + 4.

### Treatment registry

During the trial, both treatments are being properly registered. The commercial progesterone used (PROGGEFFIK™) is re-labelled in the Clinical Trials Pharmacy Unit of the University Hospital Puerta de Hierro - Majadahonda and then distributed to all participating centers. The label includes the following data: trial code, sponsor name, investigational product, batch number, expiration date and the trial subject identification number. Regarding the pessary, the batch number and the expiration date also are being registered.

### Study outcomes

The primary outcome measure is the proportion of spontaneous preterm birth before 34 weeks of gestation. The secondary outcomes are the following: proportion of spontaneous preterm birth before the 37th and 28th weeks, the rate of premature rupture of membranes before 34 weeks, the neonate’s weight at birth, the rate of fetal intrauterine mortality during the treatment period, the rate of neonatal morbidity and mortality, the need for hospitalization and tocolysis treatment, the rate of chorioamnionitis during the third term, symptomatic vaginal infections during the treatment period and the proportion of participants with adverse events.

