### Study population and trial development

Pregnant women with a short cervix (≤25 mm) as identified by routine transvaginal ultrasonography at 19 to 22 weeks of gestation are eligible to enroll. Before the evaluation, the woman should have an empty bladder and be placed in the dorsal lithotomy position. The vaginal probe should be placed in the anterior fornix without pressure. Initial orientation is established by locating the sagittal view of the cervix. The length of the endocervical canal should be measured in a straight line from the internal to the external cervix. The cervix is dynamic; therefore, three measurements should be made over a 3-minute period, and the shortest measurement reported for clinical use [16, 38]. During this routine ultrasonography in the second term, singleton-pregnancy women with a short cervix (≤25 mm) are considered to participate in the PESAPRO trial. Table 1 shows the inclusion and exclusion criteria. A member of the research team informs the patient about the clinical trial during this (second trimester ultrasound) visit or at a different time, according to investigator criteria. Once informed consent has been obtained and baseline data has been collected (demographic, medical and obstetric history, vaginal and endocervix samples for culture), participants are individually randomized to vaginal progesterone or pessary. Study participants are evaluated every four weeks (±7 days) for a total of four visits; routine assessments (such as blood pressure, and weight), cervicometry and fetal ultrasonography are performed during each visit to assess adverse events and compliance with the study medication (in the progesterone group). Women are asked to return unused study medication from the previous 4 weeks and compliance is determined on the basis of the amount of the study drug that is unused. Study treatments continue until the third term (37 to 37 + 4 weeks), when the obstetrician removes the pessary, collects all the leftover medication, or until delivery, whichever occurs first.

**Table 1 Tab1:** Inclusion and exclusion criteria for PESAPRO

Inclusion criteria	Exclusion criteria
• Women older than 18 years old	• Major fetal and/ or uterine abnormalities
• Pregnant women with a short cervix (<25 mm) identified by the use of routine transvaginal ultrasonography at 19 to 22 weeks of gestation	• Placenta previa during current pregnancy

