• Gestational age at randomization between 20 weeks + 1 and 23 weeks +6	• Vaginal bleeding or ruptured membranes in the moment of randomization
• Single pregnancy	• Cervical cerclage *in situ*
• Women sign informed consent according to the GCP and local legislation	• History of cone biopsy
	• History of three or more premature labor
	• Allergic to peanut
	• Contraindication for progesterone usage
	• Active treatment with progesterone at randomization
	• If in an investigator’s opinion, there are findings on physical examination, abnormalities in the results of clinical analyzes or other medical factors, social or psychosocial that could negatively influence
	• Women unable to give the informed consent

Any patients who develop preterm labor during the study are treated according to the standard practice of the participating institution. The study treatments continue during hospitalization until the moment at which delivery is unavoidable or until completion of gestation is indicated. One additional assessment (medical record review or phone call) is performed 4 to 6 weeks after delivery in order to collect full data. See Table 2 for the detailed schedule of enrollment and assessments.

**Table 2 Tab2:** Schedule of PESAPRO study’s visit

	Visit 1 (Routine control 2 term)^a^	Inform Visit	Visit 0 basal (20 weeks + 1 to 23 weeks + 6)	Visit 1 (V0 + 4 weeks)	Visit 2 (V1 + 4 weeks)	Visit 3 (V2 + 4 weeks)	Visit 4 (EOT) (37 weeks to 37 weeks + 4)	Post-delivery visit (4 to 6 weeks post-delivery)
Eligibility criteria		**√**	**√**					
Informed consent			**√**					
Randomization and start of treatment			**√**					
Blood pressure/ weight			**√**	**√**	**√**	**√**	**√**	
Vaginal culture			**√**					
Manual vaginal exam			**√**				**√**	
Cervicometry	**√**		**√**	**√**	**√**	**√**	**√**	
Follow-up Questionnaire				**√**	**√**	**√**	**√**	
Basic fetal US			**√**	**√**		**√**	**√**	
End of treatment (EOT)							**√**	
Review maternal medical history			**√**					**√**
Review neonate medical history								**√**

^a^This visit is a routine (“standard of care”) visit in the control of pregnancy. Patients with a short cervix are invited to an extra visit (for information) before being enrolled in the study

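### Chorioamnionitis is counted only in an inconsistently defined third term, so part of the treated time after randomisation falls outside the comparison

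*Protocol article*

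**What the plan says.** The Study outcomes section of the Protocol article includes "the rate of chorioamnionitis during the third term" among the secondary outcomes. The same sentence uses a wider window for two neighbouring outcomes: "the rate of fetal intrauterine mortality during the treatment period" and "symptomatic vaginal infections during the treatment period". It also lists "proportion of spontaneous preterm birth before the 37th and 28th weeks" and "the proportion of participants with adverse events".

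Table 1, under Study population and trial development, fixes the start of exposure: "Gestational age at randomization between 20 weeks + 1 and 23 weeks +6". Table 2 places randomisation and start of treatment at that same visit.

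The article uses *term* in two ways. In Study population and trial development it writes "During this routine ultrasonography in the second term" for the second-trimester scan, which suggests that a term is a trimester. The same section then says "Study treatments continue until the third term (37 to 37 + 4 weeks", which ties the third term to a few days at the end of treatment. No other part of the article defines the third term or widens the chorioamnionitis window.

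**The concern.** The window opens some weeks after treatment begins. A woman who develops chorioamnionitis and delivers before it opens cannot have the outcome as written. Two problems follow.

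- **Completeness.** The rate leaves out cases that arise under treatment early in the course. The Background raises chorioamnionitis when it discusses pessary safety, so the comparison is relevant to the trial's own safety questions.
- **Comparability.** To be at risk of a third-term event a woman must still be pregnant at the start of the window, and prolonging pregnancy is what both treatments are meant to do. The article states no denominator for this rate. If all randomised women are counted, in line with the intention-to-treat principle, an early case stays in the denominator as event-free. If women already delivered are left out, the comparison is conditioned on something that happened after randomisation. In neither case is the result a full comparison of the randomised groups.

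This is a stated restriction, not a detail left to a fuller document, and the article gives no reason for treating this outcome differently from its neighbours.

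**Working it through.** **The plan's own figure.** The article states no figure for this outcome. Its sample size was reproduced to see whether the point touches it. With rates of 6 % and 12.4 %, a 4 % margin, one-sided alpha of 2.5 % and 80 % power:

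n per arm = (1.960 + 0.842)² × (0.06 × 0.94 + 0.124 × 0.876) / (0.124 − 0.06 + 0.04)² = 7.85 × 0.1650 / 0.0108 ≈ 120.

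Allowing for 5 % drop-out, 120 / 0.95 = 126.3, so 127 per arm and 254 in total, as stated. The chorioamnionitis window does not enter this calculation.

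**Inputs for the window.**
- Entry: 20+1 (day 141) to 23+6 (day 167), from Table 1.
- End of planned treatment: 37+0 (day 259) to 37+4 (day 263), from Study population and trial development.
- Start of the third term: not given as a trimester boundary. Assumed 27+0 (day 189) or 28+0 (day 196), with the article's gloss of 37+0 (day 259) as the other reading.

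**Formula.** Days left out = start of window − entry. Share left out = days left out / (end of treatment − entry).

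| Window opens | Entry | Days left out | Share of treatment to 37+0 | Share to 37+4 |
|---|---|---|---|---|
| 27+0 | 23+6 | 22 | 22/92 = 23.9 % | 22/96 = 22.9 % |
| 27+0 | 20+1 | 48 | 48/118 = 40.7 % | 48/122 = 39.3 % |
| 28+0 | 23+6 | 29 | 29/92 = 31.5 % | 29/96 = 30.2 % |
| 28+0 | 20+1 | 55 | 55/118 = 46.6 % | 55/122 = 45.1 % |
| 37+0 | 23+6 | 92 | 92/92 = 100 % | 92/96 = 95.8 % |
| 37+0 | 20+1 | 118 | 118/118 = 100 % | 118/122 = 96.7 % |

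**How many women this could touch.** These are shares of planned time, not of cases. The article gives no chorioamnionitis rate and no planning rate for birth before 28 weeks, so the number of missed cases cannot be derived. The planning rates for birth before 34 weeks give a loose ceiling on the number of women delivered by 28 weeks: 0.06 × 127 = 7.6 in the pessary arm and 0.124 × 127 = 15.7 in the progesterone arm. On the trimester readings, the number delivered before the window opens lies somewhere between none and these figures. On the 37-week reading, all of them are delivered before it opens.

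**The case against.** The strongest reply is that early cases are not lost to the trial. All adverse and serious adverse events are recorded (Coordination and conduct of the trial), the proportion of women with adverse events is itself an outcome, and maternal and neonatal histories are reviewed after delivery (Table 2). A case ending in spontaneous birth at 25 weeks also counts in the primary outcome and in the outcome for birth before 28 weeks, so an arm with many such cases would look worse there. All of this stands, and it limits the damage to one secondary comparison. It does not repair that comparison: a proportion with any adverse event says nothing specific about chorioamnionitis.

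A second reply is that a condensed article leaves operational definitions to the full protocol. That would excuse a missing definition of the third term. It does not excuse a stated window that starts later than treatment.

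Some stronger readings are tempting but not supported:

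- A reader might infer that every chorioamnionitis leading to birth before 28 weeks is excluded. That holds if the window opens at 28+0 or at 37+0, but with a start at 27+0 a case in week 27 would count. The article does not state the trimester boundary.
- A reader might infer that this hides the main harm of a vaginal device, or favours the pessary. The article ranks no harm in this way, and the Background reports no increase in chorioamnionitis with the pessary. At the planning rates early births are more frequent under progesterone, so missed cases could equally flatter that arm.
- A reader might infer that fetal deaths after early stopping of treatment are also missed. This needs the treatment period to end when an individual woman stops. The article does not say so; it describes treatment as running to 37 to 37+4 weeks or delivery and analyses by intention to treat.

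**Conclusion.** The point holds for this one secondary outcome. As written, the chorioamnionitis rate omits 22 to 55 days of treated time after randomisation, about 24 to 47 % of the planned course to 37+0, if the third term means the third trimester. That range assumes a trimester start at 27+0 or 28+0. Under the article's own gloss the omission is about 96 % or more. The trimester reading is the more natural one given how the article uses second term, but the fact that the text supports readings so far apart is itself a reason to correct it.

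The direction and size of any bias between arms cannot be stated from the document. What can be stated is that the comparison is incomplete and depends on pregnancy continuing to the start of the window. The primary analysis and the sample size of 254 stand as they are.

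**What to change.** Define the outcome as any chorioamnionitis from randomisation to delivery, with all randomised women in the denominator. If a third-trimester rate is still wanted, report it as a supplement, with the starting gestational age and the denominator stated. Use one meaning of *third term* throughout, so that it no longer denotes both a trimester and the 37 to 37+4 week visit.

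The cost is a change of outcome wording. Table 2 already schedules a review of the maternal history 4 to 6 weeks after delivery, and adverse events are already recorded, so no extra visit is needed and the sample size does not change.

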Finally, regarding safety, it is worth highlighting that natural, micronized vaginal progesterone is a medicine that can be administered either orally or vaginally. There are no described adverse reactions in the product monograph when it is administered vaginally. Some women have reported a slight increase in vaginal discharge [36]. Cervical pessary can produce an increase in vaginal discharge, but without an increase in bacterial vaginosis or corioamnionitis in pregnant women. Although slight discomfort can sometimes occur during pessary placement, most patients note that the discomfort is acceptable [30].

Because of the published data, ultrasound measurement of the cervix is being progressively incorporated into clinical practice and either pessary or progesterone is increasingly being used in women with a short cervix. However, there is a “therapeutic hole” and neither of the two strategies is approved for this indication. In order to clear up any doubts about the potential benefits of both treatments and to establish clinical recommendations, comparative data are necessary. Alfirevic et al. [37] compared three different cohorts using cervical pessary, vaginal progesterone or cerclage for women with a singleton pregnancy and a high risk of preterm birth due to a prior spontaneous preterm birth before 34 weeks and a shortened cervical length as detected by transvaginal ultrasound. Their data suggests that the three treatments are a reasonable option in this population and they concluded that direct randomized comparisons of these strategies are needed.

The main objective of the PESAPRO trial is to compare the efficacy of two treatments, vaginal progesterone and cervical pessary, in terms of decreasing the rate of spontaneous preterm births before 34 weeks of gestation in women with a short cervix, which has been detected by transvaginal ultrasonography.

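### The chorioamnionitis outcome is counted only in the 'third term', so cases in the first weeks of treatment cannot enter the named comparison between arms

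*Protocol article*

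**What the plan says.** The Study outcomes section of the protocol article lists the secondary outcomes in one sentence. Chorioamnionitis appears as "the rate of chorioamnionitis during the third term". Two other outcomes in that sentence have a window matched to exposure: "the rate of fetal intrauterine mortality during the treatment period" and "symptomatic vaginal infections during the treatment period". The sentence also includes the "proportion of spontaneous preterm birth before the 37th and 28th weeks", so births before 28 weeks are expected and counted.

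Table 1 sets the start of exposure: "Gestational age at randomization between 20 weeks + 1 and 23 weeks +6". Table 2 puts randomisation and start of treatment at the same visit. The end of exposure is given under Study population and trial development: "Study treatments continue until the third term (37 to 37 + 4 weeks), when the obstetrician removes the pessary", or delivery if that comes first. This is the only place where the article attaches dates to 'third term'.

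The Background section raises chorioamnionitis when it summarises pessary safety. It says that a pessary can increase vaginal discharge, "but without an increase in bacterial vaginosis or corioamnionitis in pregnant women".

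**The concern.** An infection outcome that is meant to compare two vaginal treatments should cover the time during which women are exposed to them. This one opens some weeks after treatment starts, although the authors used a treatment-period window for vaginal infections in the same sentence. The article gives no reason for the difference.

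The restriction also interacts with the event under study. Whether a woman reaches the window depends on her pregnancy continuing, which both treatments aim to influence. A woman with chorioamnionitis who delivers before the window opens cannot be a case. The article raises chorioamnionitis as a pessary safety matter and intends the trial to inform clinical recommendations, so its own comparison on this point should not omit the first part of exposure.

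**Working it through.** **Inputs.** Start of treatment: 20+1 to 23+6 weeks (Tables 1 and 2). End of treatment: 37+0 to 37+4, or delivery if earlier (Study population and trial development; Study interventions). Start of the third trimester: not defined in the article, so 28+0 is assumed, with 27+0 and 29+0 as alternatives.

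**The plan's own figure.** The article gives no expected chorioamnionitis rate, so there is no figure to reproduce for this outcome. The sample size belongs to the primary outcome and does reproduce. With assumed rates of 6 % and 12.4 %, a 4-point margin, one-sided alpha of 2.5 % and 80 % power, the distance to the margin is 12.4 − 6 + 4 = 10.4 points. Then n = (1.960 + 0.842)² × (0.06 × 0.94 + 0.124 × 0.876) / 0.104² = 120 per arm after rounding up. Allowing for 5 % drop-out, 120 / 0.95 rounds up to 127 per arm, or 254 in total. Nothing below changes it.

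**Uncounted share of planned treatment time.** Share = (start of window − randomisation) / (37+4 − randomisation), in days. The denominator is 122 days for entry at 20+1 and 96 days for entry at 23+6.

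| Assumed start of window | Entry at 20+1 | Entry at 23+6 |
|---|---|---|
| 27+0 | 48/122 = 39 % | 22/96 = 23 % |
| 28+0 | 55/122 = 45 % | 29/96 = 30 % |
| 29+0 | 62/122 = 51 % | 36/96 = 38 % |

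Ending the clock at 37+0 instead gives 55/118 = 47 % and 29/92 = 32 % for the 28+0 start. If it runs to a delivery at 40+0 (assumed), the figures are 55/139 = 40 % and 29/113 = 26 %.

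**What happens to a case before the window.** The Statistical analysis section adopts intention to treat and Fisher's exact test for categorical variables, but gives no denominator for this outcome. There are two possibilities.

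1. All randomised women are in the denominator. A woman with chorioamnionitis who delivers before the window opens counts as infection-free.
2. Only women still pregnant when the window opens are in the denominator. Her case disappears, and the arms are compared in subsets selected after randomisation.

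Under neither does the case appear in the named comparison.

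**Meaning of 'third term'.** The article uses *second term* for the second trimester in Participating centers, in Study population and trial development and in Table 2. Third trimester is therefore the likely meaning, and the calculation rests on it.

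**The case against.** The strongest reply is that little is really lost. All adverse events and serious adverse events are recorded (Coordination and conduct of the trial), and the proportion of women with any adverse event is itself an outcome. Births after early infection enter the time-to-delivery analysis and, if spontaneous, the outcomes for birth before 34 and 28 weeks. Neonatal morbidity and mortality are also compared. This stands: the data need not be lost, and what suffers is one secondary comparison. It does not remove the point, because the overall adverse-event proportion pools early chorioamnionitis with every other event.

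It can also be said that the phrase is merely loose. If so, a correction is easy. As written, it sets a counting rule that contrasts with the treatment-period wording beside it.

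A reader might infer stronger conclusions that the documents do not support:

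- *That the window is only 37+0 to 37+4, so no preterm birth could ever count.* The dates in Study population and trial development mark the end-of-treatment visit, and the use of *second term* points to trimesters. The phrase needs clarifying, but that reading is unlikely.
- *That early cases are definitely scored as infection-free.* The denominator is not stated.
- *That the comparison is biased towards no difference, or reversed.* That would need the arms to differ in chorioamnionitis before the window opens, and the article gives no basis for assuming this.
- *That 30 % to 45 % of cases are missed.* The article gives no distribution of chorioamnionitis over gestation, so the shares describe time only.
- *That infection is the main safety concern with the pessary.* The Background section mentions chorioamnionitis but does not rank it.

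**Conclusion.** The point holds as a defect in the definition of one secondary outcome. The stated window leaves out the first weeks of treatment, and a case that ends in birth before the window opens cannot count in the chorioamnionitis comparison, whichever denominator is used. No other part of the article extends the window or justifies it.

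Read as third trimester from 28+0, the window misses about 30 % to 45 % of planned treatment time to 37+4, and 23 % to 39 % if it starts at 27+0. The start of the trimester is an assumption. The number of cases affected and the direction of any distortion cannot be worked out from the article. The noninferiority comparison and the sample size of 254 are not affected.

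**What to change.** Define the outcome as chorioamnionitis from randomisation to delivery, with all randomised women in the denominator. If the sponsor wants to keep the third-trimester view, tabulate cases by onset before and from 28 weeks as a supplement. State what 'third term' means in gestational weeks, so that the outcome definition and the dating of the end-of-treatment visit no longer use one phrase in two ways.

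Recruitment began in August 2012, so this is a change to a running open-label trial. It needs a minor protocol amendment with ethics review and a registry update, as the Ethical considerations section provides for relevant amendments, and a changed derivation rule. It should be made without reference to results by arm. No visit or test is added, because adverse events are already recorded and Table 2 already schedules a maternal record review 4 to 6 weeks after delivery.
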